# Shared care management of patients with type 2 diabetes across the primary and secondary healthcare sectors: study protocol for a randomised controlled trial

**DOI:** 10.1186/s13063-016-1409-y

**Published:** 2016-06-04

**Keywords:** Diabetes care, Diabetes complications, Randomised controlled trial, Risk stratification, Shared care, Type 2 diabetes

## Abstract

**Background:**

The prevalence of type 2 diabetes (T2D) is growing globally and hospital-based outpatient clinics are burdened with increasing numbers of patients. To ensure high quality treatment and care, it is necessary to structurally reorganise the management of patients with T2D. The objective of this study is to test if T2D patients (who are at intermediate risk of or are already having incipient diabetic complications) jointly managed by a hospital-based outpatient clinic and general practitioners (shared care programme) have a non-inferior outcome compared to an established programme in a specialised (hospital based) outpatient diabetes clinic.

**Methods:**

The study is designed as a randomised controlled trial. The shared care model will be tested during a period of 3 years, with data collection at baseline and at 12, 24 and 36 months. All patients will be offered four medical visits a year; the shared care intervention consists of one annual comprehensive check-up at the outpatient clinic and three quarterly visits at the general practitioners’ office. The control group will be followed with four quarterly visits at the outpatient clinic, including an annual comprehensive check-up. In the outpatient clinic, the patients will be treated by a specialised diabetes team, including an endocrinologist. On the basis of a predefined stratification model, we will recruit patients stratified to be at intermediate risk of or already having incipient diabetic complications. We plan to include 140 patients. The primary outcome is glycated haemoglobin. Other outcome measures include (1) the proportion of patients who meet the Danish standard indicators reflecting quality of care; (2) quality of life measured by Short Form 36; and (3) the functionality of the patients’ families measured by Family Assessment Measure III. The experiences of the patients and families when participating in the shared care program will be explored by collecting dyadic interviews.

**Discussion:**

This study will evaluate the quality of a shared care programme for patients with T2D, and provide evidence about advantages and disadvantages compared with a programme in a specialised outpatient clinic. The results may provide important information on how to organise the care for patients with T2D in the future.

**Trial Registration:**

This trial was registered with Clinicaltrials.gov on 21 October 2015, registration number: NCT02586545.

**Electronic supplementary material:**

The online version of this article (doi:10.1186/s13063-016-1409-y) contains supplementary material, which is available to authorized users.

## Background

The incidence and prevalence of type 2 diabetes (T2D) are increasing globally [1–3]. T2D is a multifactorial and chronic disease associated with serious complications and co-morbidities, and it is among the 10 leading causes of death worldwide [4, 5]. The number of adults with diabetes is estimated to rise by 55 % during a 22-year period, from 382 million individuals in 2013 to 592 million individuals in 2035 [2, 3]. Compared to the general population, patients with T2D have increased morbidity and mortality [6–8] due to an increased risk of microvascular complications and macrovascular disease [4]. Living with diabetes is also associated with major psychosocial implications and impaired quality of life [9, 10]. Furthermore, the disease causes considerable socioeconomic expenditures and healthcare costs, especially with emerging and manifest complications to the disease [3, 11, 12]. In order to prevent or delay diabetic complications, it is essential to stabilise and treat hyperglycaemia, elevated blood pressure and dyslipidaemia [13–15]. The treatment targets for these indicators are defined in evidence-based guidelines, but treatment goals are too often not achieved [16, 17]. The increasing prevalence of T2D also challenges the healthcare systems in terms of how to prioritise the limited resources. Therefore, the need for considering alternative organisational models for the management of T2D, ensuring high quality care, is urgent.

During the last decades, numerous models of diabetes management have been evaluated; among these are shared care models [18, 19]. Shared care can be defined as a joint delivery of care conducted in cooperation between general practitioners (GP) and medical specialists [20]. In most shared care models, the GP is guided in the management of T2D on the individual patient level by the specialised team [21–24]. Thus, the patient may benefit from the broad knowledge of the GP and the expertise of the medical specialists. Furthermore, there may be economic savings for the community as visits at hospital-based outpatient clinics, in general, are more expensive than GP visits. The challenges of shared care may be the difficulty in keeping track of the patients’ visiting schedule in the transition from one healthcare sector to another and potential loss of information across the interface of the primary and secondary healthcare sectors. Moreover, there is a risk of dilution of responsibility for the individual patient among the different healthcare professionals, potentially leading to ineffective decision-making and care. According to a previous Cochrane review, insufficient favourable evidence was found to support shared care programmes for patients with chronic diseases [20]. This conclusion, however, is limited by the interventions being complex and multifaceted as well as the methodological shortcomings and inadequate length of follow-up of the studies included in the review. Furthermore, the review did not test shared care programmes specifically for patients with T2D, but for chronic diseases in general.

An Australian observational study tested a community-based T2D management programme run by specially trained, primary care physicians, who were supported by an on-site endocrinologist [23]. They found a significant decrease in glycated haemoglobin (HbA_1c_) among patients in the intervention group at 12-months’ follow-up, but no change among patients in the control group. The latter consisted of patients in long-term follow-up at the outpatient clinic. However, this result may be biased because of lack of randomisation, as the intervention was not offered to all patients, but only to those who were referred by their GP to the outpatient clinic during the study period. Furthermore, the patients in the intervention group had significantly higher HbA_1c_ than the control group at baseline, but at 12-months follow-up the HbA_1c_ was similar in the two groups. In an Irish trial [24], general practice clinics were randomised to conduct either usual care or shared care to patients with T2D. Shared care consisted of educational programmes for healthcare professionals in the general practices, as well as an annual diabetes review performed in a specialised outpatient clinic. They found no significant differences in HbA_1c_ at 18-months follow-up.

Future studies testing the effectiveness of shared care interventions are recommended to be developed within research settings and also with high-quality design, well-defined interventions, and with an extended length of follow-up period [20]. According to Danish regional guidelines, patients with T2D in intermediate risk for progress of diabetic complications, identified via a risk stratification model, are recommended to be followed in tight collaboration between GP and specialised and hospital-based outpatient clinics [25]. In line with these recommendations, we plan a randomised controlled trial to test a shared care model in a well-defined group of patients with T2D, with well-defined transition and decision making across the healthcare sectors.

## Methods/Design

### Study design

The present trial is a proof-of-concept study. We aim to test the effect of a new model of organisation and management of diabetes care, and compare it with a standardised care management programme in a specialised outpatient clinic. The study is designed as a randomised controlled trial testing for non-inferiority between the two programmes. We hypothesise that patients with T2D followed in a shared care programme (intervention) will have a comparable primary outcome (HbA_1c_) compared to patients receiving standard care (control). The study flow is indicated in Fig. 1. The study follows the guidelines of Standard Protocol Items: Recommendations for Interventional Trials (SPIRIT) (Additional file 1).

**Fig. 1 Fig1:**
[figure not shown]
Study flow diagram. The planned flow of participants through the different stages of the study

### The settings

The study is a cross-sectional study with several settings. The intervention takes place in the diabetes outpatient clinic at Gentofte Hospital, University of Copenhagen, Hellerup, Denmark, as well as in a number of general practices in the Capital Region of Denmark. The control group is managed solely in the outpatient clinic at Gentofte Hospital placed in northern Copenhagen, Denmark. Gentofte Hospital covers four municipalities with a total population of approximately 224,000 inhabitants, and with approximately 10,000 inhabitants diagnosed with diabetes [22, 23]. There are 106 general practices located in the four municipalities with a total of 150 GPs. The hospital-based outpatient clinic is staffed by a diabetes team consisting of endocrinologists with special interest in diabetes, diabetes nurses, a dietician, podiatrists, and trained nurses who perform fundus photography, which are evaluated by ophthalmologists. Currently, the diabetes team is responsible for the care of approximately 1200 patients with T2D.

### Participants

We will recruit eligible patients followed for T2D by either their GP or at the outpatient clinic. A patient is only eligible if their GP accepts participation in the study. Therefore, we will recruit GPs before recruiting study participants. Invitations to participate will be distributed by mail to all regional GPs referring patients to Gentofte Hospital. We intend to include approximately 25 GPs, aiming at recruiting six patients from each practice or until we have reached the predefined number of patients in the study (n = 140). An endocrinologist and the primary investigator will make appointments for visiting GPs who have accepted to participate. The duration of the individual visit at the GP’s office will be of approximately 2 hours. During the visit, we will identify patients who are eligible to participate according to the inclusion criteria. Patients managed by the GP and patients previously referred from the individual GP to be managed at the outpatient clinic are identified. Thus, both patients who have their T2D managed solely by their GP, or at the outpatient clinic, will be recruited. Eligible patients will be contacted by phone and, if the patient shows interest in participating in the study, written information will be sent by regular mail or e-mail. If the patient agrees to participate in the study by giving written consent, she/he will be invited to a baseline-screening visit in the outpatient clinic (Fig. 2). If all inclusion criteria are fulfilled and none of the exclusion criteria are met, patients will then be randomised to one of the two groups. Patients who decline to participate or do not meet the inclusion criteria will continue their usual T2D care either at the GP or at the outpatient clinic.

**Fig. 2 Fig2:**
[figure not shown]
Content of the annual comprehensive check-up in the outpatient clinic

### Inclusion criteria

Patients with T2D over the age of 18 years, able to understand, speak and write Danish, willing to give oral and written consent, and at predefined risk stratification level 2, are eligible for the study. According to the risk stratification model applied (Table 1), patients with T2D can be stratified into three levels: level 1 (uncomplicated), level 2 (intermediate risk) or level 3 (high risk). The model is an organisational tool intended to graduate the medical care and treatment according to the severity and complexity of T2D. Patients stratified at level 1 have well-controlled T2D and are recommended to be followed in general practice, whereas patients at level 3 are recommended to be followed in hospital-based outpatient clinics, as they have dysregulated T2D and/or increasing severity of complications and/or co-morbidity. Patients stratified at level 2 are moderately dysregulated T2D and/or having incipient complications. These patients are recommended to be followed in closer collaboration between hospital and general practice. The model was originally defined in a report from the Capital Region of Denmark compiled by diabetes specialists, other experts and GPs [26] and based on current evidence on treatment goals and cut-off points in diabetes management [27–30]. In the present trial, the model is slightly modified to make the model more operational. In a recent study of the population in our outpatient clinic, we found that 54 % of the patients were stratified to level 2, while less than 5 % were stratified to level 1 [31].

**Table 1 Tab1:** Risk stratification model for patients with type 2 diabetes

	Level 1	Level 2	Level 3
HbA_1c_ (mmol/mol)	<53	53–75	>75
Blood pressure, systolic/diastolic (mm Hg)	<130/80	130/80–160/90	>160/90
Metabolic complications	No	Severe insulin resistance^a^	Very fluctuating plasma glucose^b^ or severe hypoglycaemia
CVD^d^	No	One previous MACE	>1 MACE, symptomatic CVD or NYHA II-IV
Diabetic foot disease	No	Peripheral neuropathy^c^ or artery disease^d^	Previous or existing ulcer or Charcot foot
Retinopathy	No or simplex retinopathy	Progression of retinopathy	Macula oedema or proliferative retinopathy
Nephropathy	No	Micro-albuminuria^e^	Macro-albuminuria^f^

All parameters in level 1 have to be fulfilled to be allocated to risk stratification level 1. At risk stratification level 2, at least one parameter has to be fulfilled in level 2, and none in level 3. Patients at level 3 have to fulfil at least one of the parameters in level 3 [16].

*HbA*
_*1c*_ haemoglobin A_1c_, *CVD* cardiovascular disease, *MACE* major cardiovascular event, *NYHA* the New York Heart Association functional classification in patients with heart disease [36]

^a^Severe insulin resistance: Insulin dose > 2.0 U/kg/day

^b^Very fluctuating plasma glucose: Daily plasma glucose values of > 15 mmol/L or < 5 mmol/L

^c^Peripheral neuropathy: Vibration perception threshold ≥ 25 mV evaluated by a biothesiometer

^d^Peripheral artery disease: Ankle-brachial index < 0.9 with or without symptomatic claudication

^e^Micro-albuminuria: > 1 occasion of urine albumin/creatinine ratio between 30 and 299 mg/g

^f^Macro-albuminuria: Urine albumin/creatinine ratio ≥ 300 mg/g or an estimated glomerular filtration rate < 45 mL/min

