### Study data

All study data will be collected in connection with the annual comprehensive check-up in the outpatient clinic at the baseline-screening visit, as well as 12, 24 and 36 months after baseline. Data will be obtained from medical records, laboratory databases, self-reported patient questionnaires and face-to-face by the primary investigator who does not take part in the treatment or care of the patients. All data will be registered in an Epidata database [32]. The database is stored at Gentofte Hospital in a secure purpose-designed password-protected web-based file system.

The primary outcome is the difference in mean HbA_1c_ between the two groups measured at 12-, 24- and 36-months follow-up. The secondary outcome is the proportion of patients who meet the set of Danish standard indicators reflecting quality of care at 12, 24 and 36 months follow-up [33]. These indicators cover seven areas, including HbA_1c_, blood pressure, low density lipoprotein, albuminuria, fundus photography, foot examination, smoking status and proper treatment and control of these factors. The indicators are primarily based on process variables, but do include a few numerical variables.

Other outcomes are listed below:

*Clinical characteristics:* Blood pressure, weight and body mass index.

*Diabetes-related laboratory parameters and characteristics:* C-peptide, insulin, lipids, liver function tests, kidney function tests, electrolytes, coagulation factors, thyroid-stimulating hormone, cardiovascular biomarkers, vitamin D, urine albumin/creatinine ratio, and registration of diabetes-related medication.

*Healthcare professionals’ experiences with shared care:* A questionnaire evaluating the experiences of the participating GPs and the endocrinologists after the completion of the 12- and 36-month follow-up periods.

*Patient-reported outcomes:* Estimation of general quality of life, diabetes-related symptoms, alcohol consumption patterns as well as patients’ experiences of family network and function.

The four questionnaires used are:

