### Population size calculation

A power calculation was conducted according to criteria for non-inferiority trials [42, 43], and based on the primary outcome measure Hb_A1c_ at 12-month follow-up. The non-inferiority margin was set at 0.4 % (1 % is approximately 11 mmol/mol) based on both clinical judgement and a guideline from the European Medicines Agency identifying the non-inferiority margin for HbA_1c_ above 0.3 % (3 mmol/mol) [44]. The standard deviation of HbA_1c_ was set at 10 mmol/mol, based on a recent study on patients with risk stratification level 2 attending our outpatient clinic [31]. With a non-inferiority margin at HbA_1c_ 4.4 mmol/mol, an alpha of 0.05 and a power at 0.8, as well as an estimated dropout rate of 10 %, the sample size has been estimated to 140 participants.

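### The pooled HbA1c test is valid for the level 2 population, but may be insensitive to a margin-sized deficit confined to patients with raised HbA1c

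*Protocol article*

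**What the plan says.** Table 1 (Protocol article, Inclusion criteria) bands HbA1c for levels 1, 2 and 3 as "HbA_1c_ (mmol/mol) <53 53–75 >75". The table note makes level 1 demanding: "All parameters in level 1 have to be fulfilled to be allocated to risk stratification level 1". Level 2 is easier to enter: "At risk stratification level 2, at least one parameter has to be fulfilled in level 2, and none in level 3". The section text describes the group in the same inclusive way: "Patients stratified at level 2 are moderately dysregulated T2D and/or having incipient complications". No minimum HbA1c is set anywhere.

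Under Study data, the outcome for everyone is glycaemic: "The primary outcome is the difference in mean HbA_1c_ between the two groups measured at 12-, 24- and 36-months follow-up". The Statistical analysis section tests it with a two-sided 90% confidence interval for the difference between the arm means, one bound of which decides non-inferiority. It names no baseline covariate for this interval.

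Under Population size calculation: "The standard deviation of HbA_1c_ was set at 10 mmol/mol, based on a recent study on patients with risk stratification level 2". The remaining inputs are "With a non-inferiority margin at HbA_1c_ 4.4 mmol/mol, an alpha of 0.05 and a power at 0.8" and 10% dropout, which give 140 participants.

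**The concern.** A patient with HbA1c 46 mmol/mol and blood pressure 135/82 is eligible, although Table 1 puts that HbA1c in the level 1 band. One obvious way for weaker care to show is failure to bring down a raised HbA1c. That route is largely closed to a patient already below 53. If many such patients are enrolled and the arms hardly differ in them, the pooled difference moves towards zero, and in a non-inferiority trial that favours the study hypothesis.

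The stake is interpretation. A declaration of non-inferiority could be read as covering the moderately dysregulated patients in level 2, although a deficit as large as the margin in that group had been averaged away.

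**Working it through.** **Inputs from the article:** margin 4.4 mmol/mol; SD 10; one-sided alpha 0.05 (one bound of a 90% interval); power 0.8; dropout 10%; N = 140; 1:1 allocation. **Assumed, because the documents do not give them:** the mean HbA1c, the share f with baseline HbA1c below 53, and the difference between arms in that group.

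**1. The plan's own figure.** n per arm = 2 × (1.645 + 0.842)² × 10² / 4.4² = 63.9, so 64 per arm and 128 in total. With dropout, 128/0.9 = 143 or 128 × 1.1 = 141. The stated 140 is reproduced to within 3%. The sample size is not in question here.

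**2. Does SD 10 fit a population confined to 53–75?** The range is 22 mmol/mol wide.
- Uniform: 22/√12 = 6.35.
- Largest SD of any single-peaked distribution on the range: 22/3 = 7.33.
- Largest SD of any shape (half at each end): 22/2 = 11.

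So an SD of 10 with level 3 values excluded points to patients below 53.

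**3. How many?** For a normal distribution truncated above at 75 and solved for SD 10, the share below 53 depends on the assumed mean:

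| Assumed mean (mmol/mol) | Share below 53 |
|---|---|
| 54 | 45% |
| 56 | 37% |
| 58 | 30% |
| 60 | 23% |
| 62 | 18% |

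**4. Effect on the overall test.** With 140 × 0.9 / 2 = 63 evaluable per arm, SE = 10 × √(2/63) = 1.78. Take the difference as shared care minus control. Let the true deficit be 4.4 at or above 53, and 4.4 × k below 53. Then

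overall difference = 4.4 × (1 − f) + 4.4 × k × f

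P(declare non-inferiority) = Φ((4.4 − overall difference)/1.78 − 1.645).

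| f | Overall difference, k = 0 | P, k = 0 | P, k = ½ | P, k = 1 |
|---|---|---|---|---|
| 25% | 3.30 | 15% | 9% | 5% |
| 30% | 3.08 | 18% | 10% | 5% |
| 40% | 2.64 | 26% | 12% | 5% |
| 50% | 2.20 | 34% | 15% | 5% |

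Example, f = 40%, k = 0: (4.4 − 2.64)/1.78 − 1.645 = −0.66, and Φ(−0.66) = 0.26.

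**5. Precision in the 53–75 group.** With f = 40%, 63 × 0.6 ≈ 38 per arm remain. The 90% half-width is 1.645 × SD × √(2/38): 2.6 for SD 7 and 3.8 for SD 10.

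**6. Would a point-estimate condition protect?** One could also require the 53–75 point estimate to lie below 4.4. Simulating the k = 0 scenario, the declaration rate moves from about 15 to 15%, 18 to 18%, 25 to 23% and 34 to 28% for f = 25, 30, 40 and 50%. Once the overall interval passes, the condition is nearly redundant.

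**The case against.** **The population is intended.** The stated objective covers patients at intermediate risk or with incipient complications, and level 2 is the group recommended for closer collaboration between hospital and general practice. This stands. Nothing in the article is contradictory here, and eligibility should not change.

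**The test keeps its error rate.** A reader might take 15–34% as an inflated type I error. The documents do not support that. In those scenarios the true overall difference is 3.30 to 2.20, inside the margin, so declaring non-inferiority is correct for the outcome as defined. The figures measure insensitivity to a subgroup deficit that the protocol sets no hypothesis about.

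**Patients below 53 can get worse.** Inferior care shows as higher HbA1c, and a patient at 46 has room to rise over 12 to 36 months. This also stands: k = 0 is the extreme case, and at k = 1 there is no dilution at all.

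**The SD is weak evidence on the share.** It is a planning value from an outpatient-clinic study. The trial also recruits patients managed solely in general practice, the stratification model was slightly modified, and HbA1c at 12 months is not capped at 75. A reader might infer that the group below 53 is shown to be large. The SD supports only a non-trivial share; the 18–45% range needs an assumed mean and distribution.

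**Adjustment and subgroup estimates may be in the SAP.** They may, so their absence from the article is not the finding. What the article does fix is the combination of broad eligibility, an HbA1c outcome and an interval described as a difference of means.

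**Conclusion.** The concern holds in a limited form. Level 2 admits patients with HbA1c below 53 by design, probably in more than trivial numbers. The overall comparison is a valid one-sided 5% test for that mixed population, and N = 140 is sound on this account. By itself, however, it cannot show non-inferiority for patients with raised HbA1c.

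The size depends on two unknowns. If patients below 53 show no difference, a 4.4 mmol/mol deficit in the others passes in about 15–34% of trials for shares of 25–50%. If they show half the deficit, it passes in about 10–15% for shares of 30–50%; if they show all of it, in 5%. The result may therefore be diluted; the documents do not establish that it is.

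**What to change.** Keep the eligibility rule and the overall non-inferiority test. In the protocol or SAP:

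1. Estimate the arm difference in HbA1c from a model adjusted for baseline HbA1c instead of from raw means.
2. Report the share of patients with baseline HbA1c below 53 mmol/mol, by arm.
3. Prespecify a supportive shared care minus control difference with 90% CI in patients with baseline HbA1c 53–75 mmol/mol.
4. If the upper bound of that interval does not exclude 4.4, word the conclusion as applying to the mixed level 2 population, and not as shown for patients with raised HbA1c.

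Do not make a 53–75 point estimate below 4.4 a condition for declaring non-inferiority, since it adds almost no protection.

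The cost is wording only: HbA1c is already measured at baseline in everyone, and adjusting for it should usually narrow the main interval. The downside is the wider subgroup interval (half-width about 2.6–3.8 mmol/mol with 38 per arm), which makes a claim for patients with raised HbA1c harder to support.
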